## Abstract

There is no safe level of lead exposure. Correlations suggest that hunters harvesting wild game with lead bullets may be at risk of lead exposure through eating minute lead particles from shrapnel in their wild game. This feasibility study will determine if it is possible to conduct an interventional controlled, blinded study to evaluate if there is a causal relationship between meat harvested with lead bullets and elevated blood lead levels in those who consume the meat. This is an observational case crossover study and the primary outcome is blood lead levels. Individuals will have blood lead levels measured 2–4 days after eating one serving of meat harvested with lead bullets. At three potential washout periods these same individuals will have a subsequent blood lead level analysis. This observational study will provide the data necessary to determine the washout period and sample size for a prospective interventional study to evaluate if meat harvested with lead bullets raises blood-lead levels in those who consume the meat. This study has been approved by the Health and Disabilities Ethics Committees of New Zealand.

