**Fig. 3 fig3:**
[figure not shown]
**Required shot placement for participation in the study**. Animals harvested for this study will be shot in the area indicated by a red box. This shot placement will be validated by photographs submitted to the study coordinator and will be the primary qualifying criteria for participating in the study. (For interpretation of the references to colour in this figure legend, the reader is referred to the web version of this article.)

Meals can be prepared at individual discretion; however, the meal must include at least 85 g of minced meat per test subject. This is equivalent to ¾ cup of minced meat and is considered a standard serving. Minced meat is used to reduce variability and allow easy determination of meal portion size. This value was used as the basis of the sample size calculation.

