Formal consenting for the trial will occur via telephone and the study coordinator will work through the form with the participant. Once the pages have all been reviewed the participant will sign the consent form and return the form by mail.3.Collection of study data

Hunters will be instructed to prepare their game in the usual manner. Typically, this involves mincing meat from the front legs of the animals and processing the rear quarters of the animal into larger cuts of meat. The participants will be instructed to text the study coordinator when processing occurs and the study coordinator will confirm receipt of the text message.

Prior to the first meat being eaten from the lead-shot animal, a baseline blood lead level will be measured. When a meal is eaten from the harvested game that involves ≥85 g (∼3/4 cup) of minced meat per person, the participants will be instructed to text the approximate number of servings eaten and notify the study coordinator of having eaten the meal. Between 2 and 4 days after eating the meal, the participant will report to the clinical laboratory in their local area for blood draw and complete blood count measurement. Each day that the participants are eligible for a blood draw they will receive texts from the study coordinator. After completing the blood draw, the participants will text the study coordinator.

Once the data from the clinical laboratory have been collected the participants will be contacted by the study coordinator. The participants will be instructed to report to the clinical laboratory at 9, 18 and 27 days during the abstention period for blood lead measures. Participants will receive a weekly text to remind them about the study. At the clinical laboratory, participants will provide a blood sample and the clinical laboratory will measure lead blood levels and complete blood count according to the standard clinical protocol. These values will be reported to the study coordinator. The study coordinator will maintain records of the results as described in Data Handling and Record Keeping.

During the study the participants will be requested to provide information on any activities that week that may have exposed them to lead such as reloading ammunition or any of the study exclusion criteria.

No biological samples will be retained.4.Analyses and reporting of results

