**Fig. 5 fig5:**
[figure not shown]
**Expected results from the blood lead level measures.** Following the washout period and baseline blood lead level measurement participants will eat their lead-shot deer. Two to four days after eating lead-shot deer be asked to abstain from eating lead-shot meat and blood lead levels will be assed at 9, 18 and 27 days. These blood lead levels will allow the sample size calculation, based on the three potential washout periods, for a subsequent interventional study to be calculated.

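### Between the baseline draw and the 2–4 day draw, only mince meals of at least 85 g have their amount reported, so the measured rise need not be that of one serving

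*Protocol article*

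**What the plan says.** **Exposure.** The abstract states: "Individuals will have blood lead levels measured 2–4 days after eating one serving of meat harvested with lead bullets". Section 2.2 requires that "the meal must include at least 85 g of minced meat per test subject", which is a minimum with no maximum, and adds: "This value was used as the basis of the sample size calculation".

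**Order of events (2.5, step 3).** "Prior to the first meat being eaten from the lead-shot animal, a baseline blood lead level will be measured". When a meal with at least 85 g of mince per person is eaten, "the participants will be instructed to text the approximate number of servings eaten and notify the study coordinator of having eaten the meal". The blood draw follows 2–4 days later. No limit is given for the time from baseline to that meal.

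**Other meat from the same animal.** The same step says hunters prepare game as usual, which typically means mincing the front legs and "processing the rear quarters of the animal into larger cuts of meat".

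**Abstention.** The Introduction excludes lead-shot meat during a 27-day period but does not say on which day it starts. Section 2.2 describes the first sampling period as one in which participants are eating lead-shot meat. The Fig. 5 legend reads: "Two to four days after eating lead-shot deer be asked to abstain from eating lead-shot meat".

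**Other checks on intake.** Section 2.10 has a weekly text and a monthly call asking all participants whether they ate harvested meat that week. Step 2 of 2.5 asks at enrolment how often per week they usually eat lead-shot animals. Step 3 asks about activities that may have exposed them to lead, such as reloading ammunition.

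**The concern.** By section 2.1, the study exists to supply a washout period and a sample size for the next trial. The change from baseline to the 2–4 day draw is the effect size it hands over, and the spread of that change is the SD.

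That change reflects all lead eaten since baseline, not only the reported meal. With a blood half-life of 28–36 days (Introduction), lead from a meal a week earlier is still mostly present at the draw. If some hunters ate other cuts and others did not, their rises differ for reasons that the data do not show, and the rise cannot be expressed per serving.

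The washout curve can also be affected. The Introduction puts the peak 2–4 days after exposure, so a cut eaten the day before the draw would peak after it and alter the apparent decline to day 9. Intake that is not recorded cannot be recovered in the analysis.

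**Working it through.** **1. What is barred and what is recorded, by interval**

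| Interval | Other lead-shot meat barred? | Amount recorded? |
|---|---|---|
| Baseline to reported mince meal | No rule stated | No. The weekly text or monthly call may show that a meal took place |
| At the reported meal | Not applicable | Yes, approximate servings |
| Reported meal to 2–4 day draw | Unclear: yes if the Introduction's 27 days run from the meal; no on the Fig. 5 legend and the 2.2 wording | As described, an amount only for a further mince meal of at least 85 g |

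An earlier mince meal of 85 g or more would itself trigger the report. Unquantified meals before the reported one must therefore be larger cuts or smaller mince portions.

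**2. The plan's own figure**

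Inputs from 2.6: difference 0.074, SD 0.19, two-sided alpha 0.05, power 0.80, dependent t-test. The normal approximation is (0.19 × (1.960 + 0.842) / 0.074)² = 51.7, so 52. The exact noncentral-t calculation gives n = 54 with power 0.802, which matches the stated 54.

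**3. One extra meal (illustration)**

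Assumptions not in the documents: one extra meal g days before the reported meal, carrying a fraction f of its lead, with first-order decay. From the Introduction: half-life h = 28 to 36 days. Both meals decay equally from the reported meal to the draw, so that part cancels:

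ratio to the one-serving rise = 1 + f × 2^(−g/h)

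For g = 7, 2^(−7/28) = 0.841 and 2^(−7/36) = 0.874.

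| f | h = 28 | h = 36 |
|---|---|---|
| 1 (equal lead) | 1.84 | 1.87 |
| 0.5 | 1.42 | 1.44 |
| 0.25 | 1.21 | 1.22 |

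**4. What this does to a sample size (illustration)**

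Assume the rise is proportional to servings and start from 0.074 and 0.19.

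*Higher mean, SD held at 0.19.* Average intakes of 1.25, 1.5 or 2 servings give rises of 0.0925, 0.111 or 0.148. A study sized on these needs 36, 25 or 15 pairs. Its power for a rise of 0.074 would be 0.62, 0.46 or 0.29.

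*More spread, mean held at 0.074.* If servings have SD s between hunters, the total SD is √(0.19² + (0.074s)²). For s = 0.5, 1 or 2 this is 0.194, 0.204 or 0.241. The required n is 56, 62 or 86, and power at 54 is 0.79, 0.75 or 0.60.

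A higher mean makes the next trial smaller, and more spread makes it larger. The documents do not show which would dominate.

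**The case against.** The strongest objections, and what remains of each:

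- **Other meals are not wholly invisible.** A reader might infer that only mince meals of at least 85 g ever come to the coordinator's notice. The documents do not support that. The weekly text and monthly call in 2.10 ask about any meal of harvested meat, and servings at the mince meal are recorded. This stands. What those contacts lack, as described, is date, cut and amount.
- **Abstention may already cover the days from meal to draw.** If the Introduction's 27 days run from the meal, it does. The contrary reading rests partly on a figure legend with words missing. This stands as a reason to call that interval unclear. It does not help from baseline to the meal.
- **Equal lead per meal is generous.** Section 2.2 requires a thorax shot, while the larger cuts come from the rear quarters. This stands, so the 1.84–1.87 figure is an illustration and not an estimate.
- **The next trial may not target one serving.** The Introduction and Discussion describe it only as eating harvested meat and being bled 2–4 days later. If eating patterns are the same, the rise transferred is the relevant one. This stands against any claim that the next trial would be several-fold too small. It does not restore the link to one serving or 85 g that this article makes.
- **The article condenses a fuller protocol.** A meal-log form or a covariate could sit elsewhere. However, step 3 itself states what participants report, and the passages on abstention do not agree.

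**Conclusion.** The point holds in a limited form. Between baseline and the 2–4 day draw, the plan quantifies only mince meals of at least 85 g. It does not bar other lead-shot meat before that meal, and it is unclear about such meat after it. The measured rise therefore need not be that of the single serving in the abstract or of the 85 g on which the sample size was based, and differing intake adds to the SD.

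It would be too strong to infer that the rise is not a one-serving rise: for any hunter who ate one serving and nothing else, it is. It would also be too strong to put a multiple on the error in the next trial's sample size. That would need meal frequencies, timing, lead per meal and a fixed SD that the documents do not give, and a one-serving target that they do not set for that trial.

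The size is unknown. Under the assumptions stated, one extra meal 7 days before the reported one inflates the rise to 1.84–1.87 times with equal lead, and less if the extra meal carries less. This is worth correcting before recruitment and is not fatal to the study.

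**What to change.** 1. In 2.5, step 3, use the existing text messages to record every meal of lead-shot meat, of any cut and amount, with its date and approximate servings, from the baseline draw to the 2–4 day draw.
2. In 2.7, include total servings in that interval as a covariate, with a sensitivity analysis in hunters who report a single meal.
3. Reconcile the Abstract, the Introduction, 2.2, 2.5 step 3 and the Fig. 5 legend on whether other lead-shot meals are allowed in that interval and on which day abstention starts.

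The cost is a few more texts per hunter and one covariate. The drawback is that fewer hunters will count as cleanly single-serving, so the sensitivity analysis may be small.

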### Primary outcome and sample size determination for the feasibility study

2.6

A two-tailed dependent *t*-test was utilized to perform a power analysis and determine sample size necessary for the study. A dependent *t*-test was used for the power analysis in order to ensure sample size would not be underestimated. To address correlation and the nature of longitudinal data, a conditional linear effects model will then be utilized to determine differences in the pattern of mean blood lead level over time. A sample size calculation was performed (SigmaPlot 12.5; Systat) and the following values were assigned based on previous literature and clinical logic: Expected Difference in Means: 0.074; Expected Standard Deviation: 0.19; Number of groups: 2; Desired Power: 0.8; Alpha: 0.05. The expected mean difference is derived from preclinical data [17] and 7 day washout. This calculation resulted in a sample size calculation of 54 data points in each abstention cohort.

We expect 25% attrition from the study and therefore we will be required to recruit a total of 68 participants.

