### General study design

2.2

There are two periods of analysis for this study.1.Hunters that within 2–4 days prior to blood being drawn have eaten self-harvested wild deer shot with lead projectiles; and2.Hunters that have abstained from eating self-harvested wild deer shot with lead projectiles for specific periods of time.

Hunters in period 1 and period 2 are the same individuals; they will be consented for the study once they have harvested an animal and provide pictures of shot placement. In order to avoid bias, the investigator performing the data analyses and the laboratory staff will be blinded to the samples. The participants will know when they are submitting blood samples during the period while eating meat harvested with lead bullets and when they are submitting blood samples while abstaining from lead-harvested meat so they will not be blinded. Animals will be shot in the thorax (Fig. 3) and the hunter will provide photographs of the shot location. Hunters should process the animal according to their standard practice, including making of minced meat.

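### Recruiting 68 with 25% attrition leaves 51 participants, not the 54 the calculation requires; keeping 54 needs 72

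*Protocol article*

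**What the plan says.** Section 2.6 of the protocol article names the sizing method: "A two-tailed dependent *t*-test was utilized to perform a power analysis and determine sample size necessary for the study". The inputs are given as "Expected Difference in Means: 0.074", "Expected Standard Deviation: 0.19" and "Desired Power: 0.8", with alpha 0.05. The result follows: "This calculation resulted in a sample size calculation of 54 data points in each abstention cohort". The attrition step is one sentence: "We expect 25% attrition from the study and therefore we will be required to recruit a total of 68 participants". The formula that leads from 54 to 68 is not shown.

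Section 2.2 settles how data points relate to people: "Hunters in period 1 and period 2 are the same individuals". Section 2.5 has the participants return for blood draws at 9, 18 and 27 days. So 54 data points at a given time point means 54 retained participants.

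**The concern.** Attrition is a loss from those enrolled, so the number to recruit is the required number divided by the proportion expected to stay. The stated 68 is what results when the required number is multiplied by 1.25 instead. Under the plan's own attrition rate, the recruitment total then fails to deliver the plan's own required number, and the 80% power that number was chosen to give is missed.

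Two features of the study make this worth correcting. Retention is central to its purpose, because section 2.1 judges feasibility by participant compliance. Section 2.5 also lets hunters who will not abstain for the full period take part for 9 days or as long as they accept, so thinner data at 18 and 27 days can be foreseen. In addition, the primary objective is to set the washout period and sample size of a later trial, and the same inflation step could be carried into that larger calculation.

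**Working it through.** **Inputs (all from section 2.6):** two-sided paired t-test; difference 0.074; SD 0.19; alpha 0.05; target power 0.80; required number 54; attrition 25%; recruitment total 68. The SD is read as the SD of the paired differences, the reading under which 54 is reproduced.

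**Step 1. Reproduce 54.** The standardised difference is 0.074 / 0.19 = 0.3895. Power comes from the noncentral t distribution with n − 1 degrees of freedom and noncentrality 0.3895 × √n.

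| n | Power |
|---|---|
| 51 | 0.7787 |
| 52 | 0.7868 |
| 53 | 0.7947 |
| 54 | 0.8023 |

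The smallest n reaching 0.80 is 54, exactly as stated. The normal approximation, (0.19 × (1.960 + 0.842) / 0.074)² = 51.7, would give 52. A two-sample formula would give 104 per arm. Neither is the plan's figure, so the paired t-test is confirmed as the route to 54.

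**Step 2. Reproduce 68.**

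- Required / (1 − attrition) = 54 / 0.75 = 72. This does not give 68.
- Required × (1 + attrition) = 54 × 1.25 = 67.5, rounded up to 68. This gives 68.
- Dividing by 0.80 also gives 67.5, hence 68, but that is 20% attrition and the text says 25%.

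**Step 3. What 68 delivers at 25% attrition.**

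- Retained: 68 × 0.75 = 51.
- Shortfall: 54 − 51 = 3.
- Paired t-test power at 51: 0.7787, against 0.8023 at 54, a loss of about 2.4 percentage points.
- Largest attrition at which 68 still yields 54: 1 − 54/68 = 20.6%.

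**Step 4. Check the corrected figure.** 72 × 0.75 = 54.

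**Step 5. Could separate cohorts rescue 68?** No. Section 2.2 says the same people supply both periods. If the abstention cohorts were different people, 54 in each would need far more than 68.

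**The case against.** The arithmetic is not in dispute. The case on the other side concerns how much it matters and which number is wrong.

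- **The inputs are softer than the error.** Section 2.6 bases them on earlier literature and clinical logic, with the difference taken from preclinical data. At n = 54, an SD of 0.196 instead of 0.19 already lowers power to about 0.78. As an illustration, SDs from 0.17 to 0.21 move power at n = 54 from 0.88 to 0.72. Three participants lie well inside that range. This stands as a comment on size. It does not excuse a figure that fails to follow from its own premises.
- **The t-test is not the planned analysis.** Section 2.7 plans a repeated-measures model over five time points, and section 2.9 fits it by REML and keeps participants with missing data. People who leave early may still contribute samples, so 77.9% describes a complete-case paired t-test and not the planned model, whose power the document does not give. This also stands. But section 2.6 chose the t-test as a safeguard against too small a sample and applied the attrition allowance to its result, so the allowance has to be right on those terms.
- **Power is not the main deliverable.** The study is meant to inform a washout period and a later sample size. With 51 instead of 54 at a time point, a standard error grows by about 3% (√(54/51) = 1.029). Nothing shows that a feasibility conclusion would change.
- **The multiplication by 1.25 is inferred.** The faulty number could be the 25% and not the 68, since 20% attrition also leads to 68. That is fair, and it is why the fix offers more than one route. The mismatch holds however 68 was reached.

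**Conclusion.** The concern holds. In section 2.6 the figures 54, 25% and 68 cannot all be right: 68 recruits with 25% attrition leave 51, and retaining 54 takes 72. The required number of 54 is confirmed and is the minimum for 80% power, so any shortfall takes the sizing calculation below its target. The size is modest: three completers, four recruits, and paired t-test power of 77.9% instead of 80.2%.

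This rests on attrition meaning loss among those enrolled, on 0.19 being the SD of paired differences, and, for the power figure only, on lost participants contributing nothing to the comparison. The planned mixed model may soften the loss of power. It does not reconcile the numbers, and no other section corrects them. The error does not invalidate the study, but a stated sample-size figure is wrong as written and should be corrected.

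**What to change.** Make section 2.6 agree with itself in one of three ways, and show the formula used:

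1. State a recruitment total of 54 / (1 − 0.25) = 72. If recruitment follows, the cost is four more hunters, each with up to five blood draws.
2. Keep 68 and state that, at 25% attrition, 51 completers are expected, with about 78% power on the paired t-test. This needs no extra enrolment, only a slightly less favourable stated power.
3. Keep 68 and state that it allows for about 20% attrition (at most 20.6%). This is open only if the lower rate can be justified.

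Whichever is chosen, use division by the retained proportion when the later interventional trial is sized.

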### Statistical methods and analysis of feasibility study

2.7

All data will be summarized using descriptive statistics (i.e. mean ± SEM). Data will be tested for normal distribution using a QQ plot and the Shapiro-Wilk test. Visualization and assessment of normality will be achieved through creation of histograms and boxplots. The primary dependent variable is mean blood lead level. In order to determine whether there is a difference in the pattern of mean blood lead level over time while accounting for lead exposure, mean blood lead level at baseline, 2–4 days, 9 days, 18 days and 27 days will be analysed using a conditional model that will account for the correlative nature of longitudinal data involving repeated measures taken from the same subject. This model is advantageous for a variety of reasons, including that this approach can handle unbalanced data (missing data at various time points), as well as continuous and discrete predictors. This model will also be able to model covariance structure which is important when handling correlated data. A random intercept will be utilized to account for natural variation in baseline blood lead measurements among hunters. Predictors will include the grouping variable of lead vs. lead-free projectile, time and the interaction of group and time. The interaction term will allow the investigators to identify whether blood lead level changes over time, thereby determining the most appropriate wash-out period. Other factors, such as any exposure to lead ammunition and isotope analysis may be included as factors in the analysis.

Categorical variables will be analyzed using chi-square tests. Variables including (agree to participate in study/decline to participate because of request to abstain/not because of request to abstain) will be used to determine the feasible length of abstaining from eating wild-shot meat. This value is important in determining the washout period for the interventional study. Adjustments using Fisher exact tests will be utilized to account for any cell counts that are 5 or less.

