**Fig. 1 fig1:**
[figure not shown]
**Design of the current feasibility study**. Participants in the current study will harvest deer with standard lead projectiles. A baseline lead measure, a measure immediately after eating the lead-shot meat, and measures at 9, 18 and 27 days. These blood lead levels will allow a model to be built determining appropriate sample size for each potential washout period.

If this current observational study determines that an interventional study is feasible, the subsequent interventional study would randomize hunters into two groups: hunters using lead projectiles and hunters using non-lead projectiles. All hunters would undergo an initial wash-out period and then have baseline blood lead level recorded. Hunters in both cohorts would then eat the harvested meat and blood lead levels would be recorded 2–4 days after eating the self-harvested meat. Hunters would then repeat this process for a replication of 3 times during the year. After one year, the hunter would cross over to the other type of projectile and repeat the entire process again (Fig. 2). This case crossover study would be analyzed utilizing a conditional linear effects model to account for the correlative nature of longitudinal data involving repeated measures. Additionally, this model will allow for other factors to be included in the model, including time-dependent covariates. Additionally it would be possible to use isotope analysis to identify if the lead levels in the blood of participants were primarily from the environment or from the lead projectiles [10], [19]. Fortunately, baseline blood lead levels in New Zealand are similar to levels in other developed countries [20] thus allowing a broad extrapolation of the data generated.

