## Discussion

4

Previous studies have established a correlation between blood lead levels and the use of lead ammunition to harvest wild game [22]. An interventional study is necessary to determine if this link between the use of lead ammunition and blood lead levels is causal. This feasibility study establishes the foundations required to conduct the necessary blinded, controlled study. The goal of this feasibility study is to determine the sample sizes necessary to determine a difference with the various washout periods.

It has been suggested that for this feasibility study including another group of participants using lead-free projectiles and randomizing these participants to the use of use lead-containing or lead-free projectiles would provide a more robust analysis. This type of interventional crossover study would conclusively determine causality and is exactly the interventional study that we propose to conduct after this current feasibility study. The feasibility study is critical to determine if this larger, more expensive, study is possible and to perform the appropriate sample size calculation.

For the subsequent crossover study (Fig. 2), a simple two period two treatment cross-over trial would be utilized. . This would allow comparison between mean blood lead levels in hunters randomized to two groups: those who eat wild game harvested with lead-projectiles versus those who do not utilize lead-projectiles. All hunters would undergo an initial wash-out period and then have baseline blood lead level recorded. Hunters would then eat the harvested meat and blood lead levels would be recorded 2–4 days after eating the self-harvested meat, at least 3 times during the year. After one year, the hunter would cross over to the other type of projectile. This case crossover approach would allow a factorial analysis of variance (ANOVA) to be conducted to determine differences in blood lead levels, while accounting for factors such as period and group (lead projectile vs. lead-free projectile).

As there is no safe level of lead exposure, determining if individuals eating wild game are exposed to lead through the self-harvested meat is an important global public health concern.

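### The feasibility model rests on a lead versus lead-free group that this study does not have, so the interaction meant to set the washout cannot be estimated

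*Protocol article*

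**What the plan says.** Section 2.7, which covers the feasibility study, plans a repeated-measures model with a random intercept for blood lead at baseline, 2–4, 9, 18 and 27 days. Its predictors are given as: "Predictors will include the grouping variable of lead vs. lead-free projectile, time and the interaction of group and time". The next sentence says what the interaction is for: "The interaction term will allow the investigators to identify whether blood lead level changes over time, thereby determining the most appropriate wash-out period".

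The design sections describe a single exposure:

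- The Fig. 1 legend: "Participants in the current study will harvest deer with standard lead projectiles".
- Section 2.2 defines period 1 as "Hunters that within 2–4 days prior to blood being drawn have eaten self-harvested wild deer shot with lead projectiles" and period 2 as "Hunters that have abstained from eating self-harvested wild deer shot with lead projectiles for specific periods of time". It adds: "Hunters in period 1 and period 2 are the same individuals".
- The Discussion takes up a comparator arm, opening with "It has been suggested that for this feasibility study including another group of participants using lead-free projectiles", and answers that such a randomised comparison is the later interventional study.

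Section 2.8, on the interventional study, contains the same predictor sentence as 2.7. Section 2.7 also allows isotope analysis as an optional factor. Sections 2.5 and 2.10 list only blood lead and complete blood count as assays, and 2.5 states: "No biological samples will be retained".

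**The concern.** Two of the three predictors named in 2.7 need a lead-free group, and the feasibility study has none. One of those two, the interaction, is the term the plan uses to choose the washout. Section 2.1 makes the washout period, together with the sample size for the next trial, the primary objective.

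The interaction is also given the wrong job. A group-by-time interaction asks whether two groups follow different time courses. Whether blood lead rises after the meal and falls during abstention in one exposed cohort is a question about the time effect. Section 2.7 lists time as a predictor but gives it no part in choosing the washout.

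**Working it through.** **Inputs**

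- Predictors: group (lead or lead-free), time, group × time (section 2.7).
- Time points: baseline, 2–4, 9, 18 and 27 days, so five levels (section 2.7).
- Exposure: lead projectiles for everyone, with the same hunters in both periods (Fig. 1 legend, section 2.2).
- Planned recruitment: 68 (section 2.6). The rank results below do not depend on this number.
- Sample-size inputs: difference 0.074, SD 0.19, two-sided alpha 0.05, power 0.80, giving 54 (section 2.6).

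**Step 1. The plan's own figure.** Section 2.6 lists two groups, so it is worth checking whether a second arm is implied.

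- Paired, normal approximation: n = [(1.960 + 0.842) × 0.19 / 0.074]² ≈ 51.7, rounded up to 52.
- Paired, noncentral t: n = 54 with power 0.802, an exact match to the stated figure.
- Two independent samples: 2 × 51.7 ≈ 103.5, rounded up to 104 per group.

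The figure of 54 is therefore a within-person comparison and gives no support for a lead-free arm.

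**Step 2. The specified model with time as five levels.** The columns are intercept (1), group (1), time (4) and group × time (4), which makes 10. With 68 hunters at 5 times there are 340 rows. If G = 1 for everyone, then

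- the group column equals the intercept column;
- G × T_k = T_k for each of the four time indicators, so every interaction column equals its time column.

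Five columns are duplicates, and the rank is 10 − 5 = 5.

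**Step 3. Variants.** For linear time the days were coded 0, 3, 9, 18 and 27, where 3 is the midpoint of the 2–4 day window (an assumption).

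| Fixed effects | Hunters | Columns | Rank |
|---|---|---|---|
| Group, time (5 levels), interaction | all lead | 10 | 5 |
| Group, linear time, interaction | all lead | 4 | 2 |
| Group, time (5 levels), interaction | hypothetical 34 lead / 34 lead-free | 10 | 10 |
| Group, linear time, interaction | hypothetical 34 lead / 34 lead-free | 4 | 4 |
| Time (5 levels) only | all lead | 5 | 5 |

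Full rank returns only when a lead-free group is added, which is the design of section 2.8. A random intercept does not alter the fixed-effects rank.

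**Step 4. Could group mean something else?** Reading it as period 1 versus period 2 contradicts the text, which names projectile type. It would not help anyway, since period is a function of the sampling day and so is aliased with time. The abstention cohorts in section 2.6 are lengths of abstention, not projectile types.

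**The case against.** No reading rescues the predictor sentence, so the case on the other side concerns how much is lost.

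- **The longitudinal analysis survives.** Section 2.7 separately states its aim as the pattern of blood lead over the five time points, and time is a listed predictor. Dropping the aliased columns leaves a model that can be fitted. This stands: the named term fails, and the data and the time effect do not.
- **The replacement is forced by the design.** Time is the only estimable predictor of the three, and this can be known before any data arrive. That largely stands, so I put no weight on the possibility of a substitute chosen after seeing the results. The choice of contrast and of how time is coded does remain open, and the text should settle it.
- **The washout has other inputs.** Section 2.7 also uses hunters' agreement or refusal to abstain, and the Fig. 1 and Fig. 5 legends promise sample sizes for each candidate washout. The refusal data show how long an abstention is acceptable, not how blood lead behaves. The sample sizes depend on the blood lead analysis. Neither replaces the faulty term.
- **Isotope analysis is only optional.** This is fair. Not keeping samples does not rule out an assay before disposal. The option has no support in the procedures described, but that is a minor aside.
- **The repair is only wording.** True, but the wording is the stated analysis for half of the primary objective.

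**Conclusion.** The concern holds. As written, the feasibility model contains five fixed-effect parameters that cannot be estimated: one for group and four for group × time. The term assigned to the washout is among them, and no sample size or software changes this. Even with a second group, the interaction would not answer the question put to it.

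The damage is confined to the stated analysis. The time effect, with four contrasts over five time points, is fully estimable. Data collection is untouched, and the stated 54 is unchanged because it already rests on a paired comparison.

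The conclusion assumes only that every feasibility participant eats lead-shot deer, as the Fig. 1 legend, section 2.2 and the Discussion all say. The text must be corrected, because the analysis it names for part of the primary objective cannot produce a result.

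**What to change.** Change section 2.7 as follows:

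1. Remove the projectile group and the group-by-time interaction, and keep both in section 2.8, where two projectile groups exist.
2. State time as the fixed effect, with the random intercept retained. Commit in advance to one coding, either the five planned occasions or elapsed days.
3. Replace the sentence on the interaction with one naming the quantities that inform the washout. With categorical time, these could be the contrasts of 9, 18 and 27 days with baseline and with the 2–4 day sample. With elapsed days, it would be the post-meal decay rate.
4. Remove the isotope factor from 2.7, since the procedures described include no isotope assay.

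The cost is a wording change. It needs no new data, visits or participants, and the sample size calculation is not affected.
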